### Instruments

The instruments are used to measure both the choices and decision making processes among patients, the acceptability of the decision aid, and feasibility of its implementation into routine clinical practice. Patient choice will be measured by the PtDA effect on their knowledge, values, and preferred choice. Decision making process will be measured by patients’ decisional conflict and preparedness to have a discussion with a healthcare professional. The primary outcome, decisional conflict scale (DCS) [37] -will be measured using the 16 item 5 response category instrument. It is robust in construct validity, reliability with a Cronbach’s alpha coefficient exceeding 0.78, and is sensitive to change when used as a single construct [38]. The scale is also subcategorized into uncertainty, informed, values clarity, support, and effectiveness. The value tool was specifically developed for the decision aid following ODSF guidelines (Additional file 1). It is a 6 item scale measuring importance placed on values associated with bowel anastomosis and permanent stoma. Answering theses value items will help clarify patient values associated with each surgical option. The choice predisposition tool looks at any inclination towards an option before and after administering the PtDA [39]. It is measured by a 15 point scale ranging from −7 (towards stoma) to +7 (towards bowel hookup). It has a test retest coefficient of 0.90 [40] and is sensitive to change in particularly the undecided participants [41-43]. The preparation for decision making tool is a 10 item scale examines a patient’s perception on how the PtDA has prepared them to communicate with practitioner [44]. This tool has a high Cronbach’s alpha coefficient of 0.92 to 0.96 and total reliability of 0.944 [45]. The acceptability tool is measured by a 7 item scale testing the comprehensibility of components of a PtDA, including its length, pace, amount of information, balance in presentation, and overall suitability [46]. This tool has face validity and has been used in at least 8 studies [46]. The decisional conflict, choice predisposition, preparation for decision making scales, and acceptability tools were obtained from the Ottawa Decision Support Group (ODSF) [47].

### Sample size

A convenience sample of patients at The Ottawa Hospital who have rectal cancer and meet the eligibility criteria will be invited to participate. A paired t-test will be used to compare the means of ‘decisional conflict’ score measured before and after the PtDA implementation. Assuming a significance level of 0.05, power of 0.80, an expected standard deviation of 0.6 [38], our required sample size is 34 to detect a clinically relevant difference of 0.3 in the decisional conflict score. The minimal clinical difference for the DCS scale was previously established because this difference is able to discriminate people who make decisions from those who delay decisions in a validation study by O’Connor [37]. Accounting for a drop out rate of 10%, our estimated sample size is 38. The study will continue until the recruitment target of 38 patients has been reached.

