In 2003, consensus standards for PtDAs were established by the International Patient Decision Aid Standards Collaboration (IPDAS) [17]. Through the Delphi method, the IPDAS involved over 100 major stakeholders such as patients, practitioners, researchers and policy makers to develop the criteria for the assessment of the quality of PtDAs. The Ottawa Decision Support Framework (ODSF) is a decision making framework informed by cognitive, social, and organizational psychological theory that guides the assessment and development of PtDAs [18]. This framework contributed to the development of the IPDAS [19]. Guidelines [20] put forth by the ODSF have been used in the development of at least 31 decision aids that were involved in 24 randomized controlled trials [21]. Adhering to quality criteria set by the IPDAS and using the ODSF as a template, a rectal cancer PtDA was developed (Additional file 1) following three principal steps: 1) A systematic review to explore the long term side effects of rectal cancer surgeries; 2) Needs assessments on rectal cancer patients and colorectal surgeons; 3) Development of a decision aid. The systematic review identified that bowel dysfunction after surgical therapies was high [22]. The needs assessments identified a lack of awareness of surgical options and their outcomes, as well as a general lack of patient involvement in the decision making process [23]. The needs assessment also identified that despite the practitioners expressing commitment to shared decision making, their view of the population to which this could apply was limited. The need for a rectal cancer decision aid was identified to encourage quality communication between patients and their practitioners. The decision aid was then designed by integrating evidence-based knowledge on the benefits and risks associated with LAR and APR. Since development, its content and presentation have been reviewed by a patient and a surgeon, but it has not been formally evaluated.

As the rectal cancer decision aid has been developed, the current study is the next step with aims to evaluate and implement the decision aid. The first phase of the proposed study will continue to follow recommendations of the ODSF to evaluate the decision aid with patients at the point of decision making [20] via a pre- and post-DA design.

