Adoption of evidence does not solely rely on the evaluation from patients, as decision making is a process that involves both the patients and the healthcare professionals. Patients’ input is necessary but their perception alone has not been sufficient to change clinical practice [24,25]. It is not surprising that even though patient decision aids may foster SDM [26,27], it has been shown that wide spread use in clinical practice has been poor [28-30]. Given the effectiveness of PtDAs, significantly more effort is needed to understand the factors preventing their integration into clinical practice [31]. The Knowledge-to-Action Cycle is a dynamic and reiterative guiding framework to outline strategies for implementation and application of knowledge [32,33]. It is a framework used by the Canadian Institutes of Health Research (CIHR) for transfer of research findings into practice [34]. It promotes the identification of potential barriers as a necessary step prior to developing an implementation strategy for the wide use of an intervention [32].

Furthermore to maintain practice change, there needs to be interventions designed to address the contextual factors that may affect the implementation [35]. A systematic review reported that the three most commonly cited barriers by health professionals are: 1) time pressure; 2) lack of SDM applicability due to patient characteristics; 3) lack of SDM applicability due to the clinical situation [24]. These results indicate that healthcare professionals in general are feeling mounting pressure from limited resources, and that practitioners may be selecting patients for SDM. This knowledge helps inform strategies for future implementation.

To address health professionals’ barriers to use the rectal cancer decision aid, the second phase of the proposed study will explore the issues perceived by the potential adopters—the surgeons working with rectal cancer patients in North America. The assessment of facilitators and barriers specific to the rectal cancer decision aid will help establish the factors associated with the healthcare professionals and the practice environment, and provide direction for selecting and tailoring implementation strategies.

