### Participants

The study will take place in a tertiary care hospital serving a population of 1.3 million people. The Colorectal Assessment Centre at the Ottawa Hospital receives on average 12 rectal cancer patient referrals per month. Approximately half (6/12) of these patients would be eligible for the study. Eligible participants are 1) patients with newly diagnosed stage I-III rectal cancer confirmed by biopsy; 2) tumor located at a maximum of 10 cm proximal to anal verge; 3) surgeon screened candidates eligible to consider LAR and APR; 4) age ≥ 18; and 5) able to understand and sign informed consent form in English. Patients with existing or previous stoma will be excluded.

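### Convenience sampling in Part 1 leaves possible patient selection unobserved, which limits the acceptability and feasibility answers and the reach of the change scores

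*Protocol article*

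**What the plan says.** The sampling method for Part 1 stands in the Sample size section: "A convenience sample of patients at The Ottawa Hospital who have rectal cancer and meet the eligibility criteria will be invited to participate". The Participants section adds a gate, since the third criterion admits "surgeon screened candidates eligible to consider LAR and APR". It sets out no further rule for that judgement, and it excludes patients who have or have had a stoma. On patient flow, the centre "receives on average 12 rectal cancer patient referrals per month", and "Approximately half (6/12) of these patients would be eligible for the study".

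The Background comments twice on how clinicians choose patients for shared decision making (SDM):
- The needs assessment done for this decision aid found clinicians committed to SDM, but "their view of the population to which this could apply was limited".
- From a systematic review of barriers cited by health professionals in general, the authors infer that "practitioners may be selecting patients for SDM".

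Recruitment takes place at the initial visit (Procedure). Feasibility is to be described by time spent on the first questionnaire and by the effect on the length of the consent visit (Secondary outcome measures). The Discussion names the missing control group and blinding as limits of Part 1 and non-response as a risk for the surgeon survey. It does not mention selection of patients into Part 1.

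**The concern.** The authors describe a way in which patients could be filtered before a decision aid reaches them. They then name a sampling method that would neither prevent that filtering nor show it. Research question 2 asks whether patients accept the aid, and question 3 asks whether it can be delivered in usual practice. Part of the answer to question 3 is who gets offered the aid at all. If some eligible patients are never approached, the study could report good acceptability and short questionnaire times while that obstacle stays out of sight.

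The changes in decisional conflict and knowledge would carry over to all eligible patients only if those not approached resemble those enrolled. A later analysis plan cannot repair this, because it does not decide who is invited, and the information is hard to rebuild once recruitment has closed.

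**Working it through.** **1. The plan's own sample size.** Inputs from the Sample size section: "Assuming a significance level of 0.05, power of 0.80, an expected standard deviation of 0.6", a difference of 0.3, and 10% dropout.
- Standardised difference, taking 0.6 as the SD of the paired difference: 0.3 / 0.6 = 0.5.
- Paired t-test, two-sided 0.05, noncentral t: the smallest n with power of at least 0.80 is 34 (power 0.808).
- Dropout: 34 / 0.90 = 37.8, rounded up to 38.

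Both stated figures reproduce. The point does not turn on them, since a larger n does not remove a selection bias.

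**2. Is consecutive invitation practical?** Inputs: 6 eligible patients a month (Participants) and a target of 38. The document gives no enrolment rate, so the rates below are assumptions. Months = 38 / (6 × rate).

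| Assumed share of eligible patients who enrol | Months to 38 |
|---|---|
| 100% | 38 / 6.0 = 6.3 |
| 70% | 38 / 4.2 = 9.0 |
| 50% | 38 / 3.0 = 12.7 |
| 25% | 38 / 1.5 = 25.3 |

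Recruitment runs until 38 are reached, and inviting everyone eligible is the fastest way to get there. These figures show that the better method is affordable. They say nothing about whether bias exists.

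**3. What could selection do to the headline change?** This is an illustration on assumed values only. Let s be the share of eligible patients enrolled, 0.3 their mean change in decisional conflict, and x the mean change the other eligible patients would have had. The mean over all eligible patients is s × 0.3 + (1 − s) × x.

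| s | x = 0 | x = 0.2 | x = 0.3 |
|---|---|---|---|
| 75% | 0.225 | 0.275 | 0.30 |
| 50% | 0.15 | 0.25 | 0.30 |
| 25% | 0.075 | 0.225 | 0.30 |

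If the others respond alike (x = 0.3), selection does no harm. If they respond more, the study understates the change: with s = 50% and x = 0.4, the mean is 0.15 + 0.20 = 0.35. The document supplies neither s nor x, so no row can be preferred. Under convenience sampling without a record of approaches, s would remain unknown after the study too.

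**4. The passages side by side.** The third criterion asks whether both operations can be considered. The two Background remarks concern who is thought to suit SDM. These are different judgements. They meet only in that the same clinicians make the first one, no stated rule bounds it, and the sampling method does not require that every patient who passes be invited.

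**The case against.** The case against has real weight.

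- **The surgeon screen tests clinical eligibility for two operations, not suitability for SDM.** The aid compares exactly those operations, so a patient without both options is outside its target population. This stands, and the criterion should stay.
- **The evidence on selection is hedged.** A reader might infer that the protocol reports clinicians choosing who receives SDM. It does not. One remark says they may be doing so and concerns health professionals generally. The other reports a limited view and no observed selection. Neither establishes selection at this centre.
- **Convenience may describe only the single accessible hospital.** On that reading, all eligible patients there might be invited, and nothing says that staff pick whom to approach. The reading is possible, but the text does not commit to it, and one word would settle the matter.
- **There are partial safeguards.** Recruitment has a fixed point, and the Discussion plans staff meetings and clinic information sheets on the entry criteria. These raise awareness, but they do not require consecutive invitation or show who was missed.
- **A screening log is detail that an article may leave to the full protocol.** Agreed: its absence here is no fault. The point rests on the sampling method that is stated, and the log is part of the remedy.
- **The main comparison is within patients, and the Discussion already disclaims causal inference.** This also stands, and it keeps the point modest.

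**Conclusion.** The concern holds in a limited form. The stated convenience method leaves room for selection that the study could not see. This restricts how far the results on acceptability, feasibility and change in scores apply beyond the patients enrolled. The within-patient change remains valid for those patients, subject to the single-arm limits that the authors acknowledge.

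A reader might go further and conclude that the results will come from a favourable subset. The document does not support that: neither the direction nor the size of any bias is shown. The illustrative means of 0.075 to 0.275 at x = 0 to 0.2 rest wholly on assumed enrolment shares and assumed responses, and other assumptions give no bias or the opposite sign.

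What can be said firmly is that consecutive invitation is the better method and that it is cheap at one centre with about 12 referrals and 6 eligible patients a month. It needs to be fixed before recruitment starts.

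**What to change.** - **Sample size section:** replace the convenience sample with all consecutive patients at the hospital who meet every eligibility criterion. This keeps the surgeon's judgement on both operations and the stoma exclusion.
- **Screening log:** for each referred patient, record the surgeon's decision on the third criterion and its reason, and then whether the patient was approached, consented or refused.
- **Reporting:** give these counts, and uptake among eligible patients, with the feasibility results.
- **Discussion:** name patient selection as a limitation of Part 1.

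The cost is a change of wording and a little clinic staff time for about 12 log entries a month. Any comparison of enrolled with non-enrolled patients should use only de-identified data that the ethics approval allows. If that approval does not cover it, the counts alone still show how much of the eligible flow was reached.

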### Outcomes

#### Primary outcome measure

The primary outcome will be decisional conflict and knowledge of surgical options. The decisional conflict scale and knowledge test will be used before and after decision aid. The mean scores will be compared using paired t-test. Knowledge test will be a score on 4 questions reflecting key points in knowledge to make decisions.

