**Methods:**

First, a pre- and post- study will be guided by the Ottawa Decision Support Framework. Eligible patients from a colorectal cancer center include: 1) adult patients diagnosed with rectal cancer, 2) tumour at a maximum of 10 cm from anal verge, and 3) surgeon screened candidates eligible to consider both low anterior resection and abdominoperineal resection. Patients will be given a paper-version and online link to the decision aid to review at home. Using validated tools, the primary outcomes will be decisional conflict and knowledge of surgical options. Secondary outcomes will be patient’s preference, values associated with options, readiness for decision-making, acceptability of the decision aid, and feasibility of its implementation in clinical practice. Proposed analysis includes paired t-test, Wilcoxon, and descriptive statistics.

Second, a survey will be conducted to identify the barriers and facilitators of using the decision aid in clinical practice. Eligible participants include Canadian surgeons working with rectal cancer patients. Surgeons will be given a pre-notification, questionnaire, and three reminders. The survey package will include the patient decision aid and a facilitators and barriers survey previously validated among physicians and nurses. Principal component analysis will be performed to determine common themes, and logistic regression will be used to identify variables associated with the intention to use the decision aid.

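### Part 1 has one primary outcome in the Instruments section but two in the Abstract and Outcomes, and the sample size covers only decisional conflict

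*Protocol article*

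**What the plan says.** Three places in the protocol article define the primary outcome of Part 1, and they do not agree.

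- Abstract, Methods: "the primary outcomes will be decisional conflict and knowledge of surgical options".
- Instruments: "The primary outcome, decisional conflict scale (DCS) [37] -will be measured using the 16 item 5 response category instrument". This names one outcome. Knowledge appears in the same section only as one of the measures of patient choice.
- Primary outcome measure: "The primary outcome will be decisional conflict and knowledge of surgical options". Both instruments are given before and after the decision aid, and "The mean scores will be compared using paired t-test".

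Secondary outcome measures does not list knowledge, so nothing there demotes it.

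The Sample size section deals with decisional conflict only: "Assuming a significance level of 0.05, power of 0.80, an expected standard deviation of 0.6", from which "our required sample size is 34 to detect a clinically relevant difference of 0.3 in the decisional conflict score". Then: "Accounting for a drop out rate of 10%, our estimated sample size is 38". No effect size, standard deviation, significance level or power is given for the four-question knowledge score.

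**The concern.** A reader cannot tell whether knowledge is a primary outcome. If it is, the sample size and its 80% power cover only half of the primary objective. If it is not, the Abstract and the Outcomes section are wrong.

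Two things are at stake. First, the meaning of the 0.05 and 0.80 in the Sample size section depends on which definition applies, and on whether one or both outcomes must be significant. Second, while the definition is open, whichever outcome turns out significant could be presented afterwards as the primary one.

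**Working it through.** **1. Reproduce the plan's own figure.** Inputs from the Sample size section: significance level 0.05, power 0.80, standard deviation 0.6, difference 0.3. Two readings are needed, and both are supported by the fact that they return the stated number: the test is two-sided, and 0.6 is the standard deviation of the paired differences.

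- Standardised effect: 0.3 / 0.6 = 0.5.
- Paired t-test, noncentral t distribution: n = 33 gives power 0.795 and n = 34 gives 0.808, so 34 are required. (A one-sided test would need 27, which does not match.)
- Dropout: 34 / 0.90 = 37.8, so 38.

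The stated 34 and 38 reproduce exactly for decisional conflict alone, with the full 0.05 spent on it.

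**2. One composite or two outcomes?** The singular noun under Primary outcome measure could suggest a single combined endpoint. But that section describes two instruments and compares mean scores, in the plural, and the Abstract speaks of primary outcomes. They are two outcomes with two tests.

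**3. If either outcome suffices, each at two-sided 0.05.** The level for knowledge is assumed.

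- Independent tests: 1 − (1 − 0.05)² = 1 − 0.9025 = 0.0975.
- Upper bound for any dependence: 0.05 + 0.05 = 0.10.
- Correlated test statistics (bivariate normal; correlations assumed, since the article gives none):

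| Correlation | Chance of at least one false positive |
|---|---|
| 0 | 9.75% |
| 0.3 | 9.5% |
| 0.5 | 9.1% |
| 0.7 | 8.3% |
| 0.9 | 7.0% |

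If 0.05 were split equally, decisional conflict would be tested at 0.025. It would then need 41 evaluable patients, and 41 / 0.90 = 45.6, so 46 recruited. At 34 evaluable, power at 0.025 is 0.713.

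**4. If both outcomes must be significant.**

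- The error rate is at most 5%, so no split is needed.
- Joint power cannot exceed the 0.808 for decisional conflict. If knowledge also has a standardised effect of 0.5 and the tests are independent (both assumed), it is 0.808 × 0.808 = 0.65.
- With 34 evaluable, knowledge has 80% power at 0.05 only for a standardised effect of about 0.50 or more.

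**5. If decisional conflict is the only primary outcome, or is tested first in a fixed order.** The level stays at 0.05, and 34, 38 and the 80% power hold for decisional conflict.

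The Sample size section fits the reading in step 5 directly. The Abstract and the Outcomes section do not state that reading.

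**The case against.** The strongest reply has four parts.

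- **The article never says that both outcomes are tested at 0.05.** This stands. The figure occurs only in the sample-size calculation for decisional conflict. A reader might infer that both tests use 0.05 and that the plan's 5% error rate therefore fails. The documents do not support that: no familywise rate is claimed, and inflation arises only if either outcome alone counts as success without adjustment, a rule the article does not state.
- **A multiplicity rule may sit in a full protocol or analysis plan that is not shown.** This also stands, so the lack of such a rule is not the finding. But no unseen document can make the Abstract, Instruments and Outcomes sections agree with one another.
- **The study is largely exploratory.** Study design speaks of exploring the effect on decisional conflict, and the Discussion concedes that a single arm without control or blinding limits causal inference. This lowers the seriousness of the point. It does not remove it, because the Sample size section sets a significance level, a power and a clinically relevant difference, and so frames a formal primary test.
- **Making knowledge secondary is a preference.** Partly so. Keeping both outcomes primary and requiring both is legitimate, provided it is stated and the power is restated.

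A reader might also suppose that knowledge is the easier outcome to move, so that it would rescue a failed trial. The Background reports that decision aids improve knowledge and lower aspects of decisional conflict, and does not rank the two.

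**Conclusion.** The article contradicts itself on whether knowledge is a primary outcome of Part 1, and its sample size matches only the single-outcome definition. The arithmetic behind 34 and 38 is correct.

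The consequence is conditional. Under an either-outcome rule with each test at 0.05, the false-positive chance would lie between about 7% and 10%, depending on an unknown correlation. Under a both-required rule, error is controlled but the stated 80% is not the power of the joint criterion; about 0.65 is illustrative and rests on independence and an assumed effect on knowledge. With decisional conflict as sole or first primary outcome, the plan's figures stand.

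This should be corrected before the data are analysed, but it is a matter of definition and does not invalidate the design.

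**What to change.** Name decisional conflict as the single primary outcome in the Abstract, Instruments and Primary outcome measure, in line with Instruments and Sample size. Test knowledge second, at two-sided 0.05, only if decisional conflict is significant; otherwise report the change in knowledge with its confidence interval as descriptive.

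This costs wording only: no further patients are needed, and 34 evaluable and 38 recruited remain valid. The downside is that a gain in knowledge could not be claimed as confirmatory if decisional conflict is not significant.

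If the sponsor prefers to keep both as primary, it should state whether one or both must be significant and restate the power in Sample size to match. An either-outcome rule with an equal split would raise the requirement for decisional conflict to 41 evaluable and 46 recruited. A both-required rule needs no split, but it does need a planning effect and standard deviation for the knowledge score.
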